#### Tertiary outcomes

##### Brain structure and function

In a subset of participants at baseline and trial completion at 6 months, MRI will be conducted at the UBC MRI Research Centre using a Philips Achieva 3.0T MRI scanner with a 32-channel sensitivity encoding head coil (SENSE factor=2.4) and parallel imaging. High-resolution structural imaging will include two three-dimensional 1-mm isotropic T1 MPRAGE (TR=2530 ms, TE=3.04 ms, TI=800 ms, flip angle=10°, FOV=256×256×220 mm) that will be averaged during post-processing and two 1-mm isotropic T2 (SPACE) images (TR=4000 ms, TE=406 ms, flip angle=90°, FOV=260×228×176 mm). T1 images will be used for co-registration of individual participant functional MRI (*f*MRI) data into a standard stereotaxic space and for ascertaining changes in cortical thickness, and cortical and sub-cortical brain volumes. To allow the assessment of white matter hyperintensities (WMHs), we will acquire two sequences of T2-FLAIR. An Automated Labeling Pathway [95] will be used to quantify volumes and localization of focal WMHs. We will also use a 60-directional diffusion tensor image with a single shot echo-planar imaging (EPI) sequence (TR=7013 ms, TE=60 ms, FOV=224×224 mm, 70 slices, 2.2-mm slice thickness, voxel dimension=2.23 mm, *b*=700 s/mm2) and 5 non-weighted diffusion weighted images (*b*=0), with a focus on measuring fractional anisotropy, mean diffusivity, axial diffusion, and radial diffusion [96]. Sixty-direction acquisition will also generate the needed resolution for fiber-tracking. Functional network organization will be evaluated with resting-state functional MRI. EPI data will be acquired with slices in an oblique 30° orientation relative to main magnetic field to optimize signal in ventral frontal regions (TR=2000 ms, TE=30 ms, flip angle=90°, FOV=220×220 mm, 3.4×3.4×3.5 mm^2^ voxels). We will collect an additional 13-min scan to maximize test-retest reliability [97]. During resting state scans, participants will be instructed to keep their eyes open, look at a fixed point on a screen, and remain awake. We will also collect a letter n-back working memory task-evoked EPI scan as well as Relational and Item Specific Encoding and Recognition task-evoked EPI scans [98]. Preprocessing of the *f*MRI data will entail rigid body motion correction, spatial smoothing, band-pass temporal filtering to exclude confounding physiological signals, followed by an Independent Component Analysis based Automatic Removal of Motion Artifacts to remove motion-related artifacts. Preprocessed resting-state time-series will be extracted from a priori selected networks of interest masks based on the Yeo 7+ Networks [99] or parcellated regions of interest based on established functional atlases and cross-correlated with every voxel in the brain to establish functional connectivity maps. For preprocessed task-based *f*MRI data, within- and between-subject differences in task-evoked neural activity will be calculated via fixed effects and mixed effects modelling.

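### At a 2 s sampling interval the fMRI band-pass cannot be relied on to exclude cardiac noise, and running it before the ICA motion removal discards frequencies that step may need

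*Protocol article*

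**What the plan says.** All references are to the protocol article, Tertiary outcomes, Brain structure and function.

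- **Acquisition.** The EPI settings are "TR=2000 ms, TE=30 ms, flip angle=90°, FOV=220×220 mm". On scan length the article says: "We will collect an additional 13-min scan to maximize test-retest reliability". Imaging is done "In a subset of participants at baseline and trial completion at 6 months"; the Exclusion criteria section puts that subset at roughly 40%.
- **Purpose of the filter.** After motion realignment and smoothing comes "band-pass temporal filtering to exclude confounding physiological signals, followed by an Independent Component Analysis based Automatic Removal of Motion Artifacts". No cut-off frequencies are given.
- **Order.** The filter is "followed by an Independent Component Analysis based Automatic Removal of Motion Artifacts to remove motion-related artifacts".
- **Use of the output.** Resting-state series are "cross-correlated with every voxel in the brain to establish functional connectivity maps". For the task scans, "differences in task-evoked neural activity will be calculated via fixed effects and mixed effects modelling".

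The preprocessing sentence follows the description of both the resting and the task scans and does not separate them. As written, one pipeline serves all fMRI data.

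**The concern.** Two stated features do not fit the acquisition.

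First, a temporal filter acts only on frequencies as they appear after sampling. A heartbeat is far faster than one volume every 2 s can follow, so it reappears at a lower, folded frequency. If that frequency lies inside the pass-band, the filter keeps it. The purpose given for the filter is then not met for cardiac noise.

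Second, an ICA-based motion classifier placed after a band-pass sees only what the filter let through. If high-frequency content is one of the features that mark a component as motion, the filter has already removed part of the evidence.

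At stake is the quality of the connectivity and task-activation measures. These serve the tertiary objective on mechanisms and could enter the planned mediation analyses. Extra noise matters more in a small imaging subset.

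**Working it through.** The article states no derived figure to reproduce, so the check is sampling arithmetic from its own TR.

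**Inputs from the article:** TR 2 s; a 13-minute scan, 13 × 60 / 2 = 390 volumes if acquired at the same TR; an imaging subset of about 40% of 216.

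**Assumptions, not in the article:** resting heart rate 50–100 bpm; several candidate pass-bands; breathing at 12–20 per minute; for the simulation, within-scan heart-rate SD of 3 bpm and an ideal 0.01–0.10 Hz filter. Only the fundamental frequency of each signal is considered.

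**1. Resolvable band.** Sampling rate = 1/2 = 0.5 Hz. Nyquist limit = 0.5/2 = 0.25 Hz, or 15 cycles per minute. The heart-rate range is 50/60 = 0.83 Hz to 100/60 = 1.67 Hz, all above the limit.

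**2. Folded frequency.** This is the distance from f to the nearest multiple of 0.5 Hz.

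| Heart rate (bpm) | f (Hz) | Appears at (Hz) |
|---|---|---|
| 55 | 0.917 | 0.083 |
| 60 | 1.000 | 0 |
| 62 | 1.033 | 0.033 |
| 65 | 1.083 | 0.083 |
| 70 | 1.167 | 0.167 |
| 75 | 1.250 | 0.250 |
| 85 | 1.417 | 0.083 |

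**3. Share of 50–100 bpm that folds into the pass-band.** For 0.01–0.10 Hz the in-band intervals are 54.0–59.4, 60.6–66.0, 84.0–89.4 and 90.6–96.0 bpm. Their total is 4 × 5.4 = 21.6 bpm, and 21.6/50 = 43%. With an upper cut-off of 0.08 Hz the share is 34–35% (lower cut-off 0.01 or 0.008 Hz). With 0.01–0.20 Hz it is 83%.

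**4. Cardiac power surviving the filter (simulated, 390 volumes, 0.01–0.10 Hz).**

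| Mean heart rate (bpm) | Share surviving |
|---|---|
| 55 | 60% |
| 60 | 79% |
| 65 | 60% |
| 70 | 8% |
| 75 | 1% |
| 80 | 9% |

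At 60 bpm the mean rate folds to 0 Hz, but ordinary variation around it spreads the power into the pass-band.

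**5. Breathing.** At 12–20 per minute the fundamental appears at about 0.17–0.25 Hz, so an upper cut-off of 0.08–0.10 Hz removes most of it.

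**6. What the ICA step loses.** With an assumed 0.10 Hz upper cut-off, (0.25 − 0.10)/0.25 = 60% of the sampled band has gone before classification. With the ICA step first, it would see the full 0–0.25 Hz.

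**7. Limit of reordering.** Changing the order does not undo the folding. Sampling 50–100 bpm without it would need a TR below 1/(2 × 0.83) = 0.6 s to 1/(2 × 1.67) = 0.3 s. At 2 s, cardiac noise needs something other than a band-pass.

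**8. Scope.** 0.40 × 216 = 86.4, about 86 participants; 86.4/4 = 21.6, about 22 per arm.

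**The case against.** Several points on the other side are sound.

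- The article speaks of physiological signals in general and never names heartbeat. The filter can remove slow drift and most of the breathing fundamental, and cardiac power too when it folds outside the band (for example 70–80 bpm with 0.01–0.10 Hz). The stated purpose is therefore partly met. This stands, and it limits the criticism to cardiac noise.
- The article does not describe which features the ICA classifier uses. That high-frequency content is one of them is a general property of the method, taken here as an assumption. Other features remain, and the loss depends on an unstated cut-off. This stands: the claim is that recognition can be weakened, and by how much is not known.
- A condensed article may leave cut-offs and nuisance regression to a fuller document. This stands, so their absence is not the finding. The finding is the purpose and the order that the article does state.

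A reader might go further and infer that aerobic training lowers resting heart rate, moves cardiac noise into the pass-band in the AT arms only, and so mimics a connectivity effect. The article does not support that. It gives a training intensity (rising to 80% of heart rate reserve, AT program section) but no resting heart rate and no expected change in any arm. The direction is not fixed either: in the simulation a fall from 70 to 65 bpm raises surviving cardiac power from 8% to 60%, while falls from 60 to 55 and from 80 to 75 lower it (79% to 60%, and 9% to 1%). How far residual cardiac power would shift a connectivity estimate has not been worked out. Noise common to all arms cancels in the randomised comparison.

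**Conclusion.** The point holds in a limited form. That heartbeat folds below 0.25 Hz follows from the article's own TR. How much falls inside the pass-band depends on heart rate and on the cut-offs: between about a third and five-sixths of the 50–100 bpm range across the bands tried. On that basis the filter should not be described as excluding physiological confounds without qualification. The order of steps is explicit and unfavourable, and the article gives no reason for it.

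Bias specific to an arm is a possibility that would need a heart-rate change differing by arm; it is not demonstrated. The consequence to plan for is avoidable residual noise in tertiary measures. The primary ADAS-Cog-Plus analysis and the sample size are untouched, and the Discussion already concedes that some tertiary outcomes will be underpowered. This is a minor point, worth making because the remedy is cheap.

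**What to change.** 1. Run the ICA-based motion removal on data that are motion-corrected and smoothed but not temporally filtered, and apply temporal filtering afterwards.
2. Reword the purpose of the band-pass so that it does not claim to exclude cardiac signal at this TR; drift and much of the breathing fundamental can stay.
3. Handle residual physiological noise with nuisance signals taken from the existing scans, for example white matter and CSF. How well these capture folded cardiac noise has not been tested here.
4. State whether the low-pass part of the filter applies to the n-back and encoding scans or to the resting-state scans only.

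The cost is a change to the processing script, reprocessing of scans already acquired, and a few degrees of freedom per scan for the nuisance signals. No new data or visits are needed. If a fuller imaging document already does this, only the article's description needs correcting.

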
##### Cardiometabolic risk factors

We will assess arterial stiffness, blood pressure, body mass index, and fasting serum glucose and lipid profile. Arterial stiffness will be measured by carotid-femoral pulse wave velocity. Pulse wave velocity will be measured using a Complior DE1210 ultrasound machine (Alam Medical, Saint Quentin Fallavier, France) with the participants lying supine and rested for at least 5 min. Resting systolic and diastolic blood pressure will be recorded in duplicate, using a voscillometric sphygmomanometer, the Omron HEM-775. Values will be presented as a mean of two recordings that are taken 1 min apart. Participants will rest seated with their back supported, feet flat on the floor, and arms supported at heart level for 5 min prior to blood pressure measurements. Body mass index will be calculated as mass in kg/height in m^2^. Fasting serum glucose and lipid profile (e.g., total serum cholesterol, triglycerides, high-density lipoprotein, low-density lipoprotein, HbA1C) will be measured by conventional laboratory methods.

##### Hypothalamic-pituitary-adrenal axis function

To assess hypothalamic-pituitary-adrenal axis activity, we will measure the stress hormone cortisol to examine (1) total cortisol concentration over the day (area under the curve); (2) cortisol awakening response, a distinct aspect of the circadian cortisol profile; and (3) changes in cortisol response to engaging in an exercise session with time of day held constant. Free cortisol levels will be assessed in salivary samples (Salivettes) collected 5× each day (at awakening, +30 min, 2 pm, 4 pm, bedtime) for 2 days at baseline and trial completion at 6 months. As well, salivary samples will be collected immediately before and immediately after the exercise session within the first 2 weeks of exercise training and within the last 2 weeks of exercise training to examine cortisol response to exercise.

##### Blood biomarkers

Fasting blood will be collected in the morning at baseline and at trial completion at 6 months from all consenting participants. Blood will be processed and stored at −80 °C as plasma, serum, and whole blood in a secure research facility. The main analytes of interest include neurotrophic factors, myokines, sex steroid hormones, and pro- and anti-inflammatory cytokines. Remaining blood samples will be stored for 5 years from collection. If there are remaining samples after 5 years and are felt to be still useful for other studies, a separate ethics application will be submitted to explain the nature of its use. Otherwise, the samples will be destroyed after 5 years from collection.

### Treatment allocation

#### Randomization

After the baseline assessment, participants will be randomly assigned (1:1:1:1) to one of four experimental groups (Fig. 1). Randomization will be performed using the “randomizeR” package in R (Uschner et al. 2018). The randomization sequence will be stratified by biological sex with equal probability (1:1:1:1) random assignment to one of the four experimental groups: (1) 4×/week balance and tone (BAT; i.e., active control); (2) combined 2×/week AT + 2×/week RT (AT+RT); (3) 2×/week AT + 2×/week BAT (AT); or (4) 2×/week RT + 2×/week BAT (RT). Permuted blocks of size 12 will be used to ensure balance. To ensure blinding, the randomization sequence will be generated away from study personnel and held in a password-protected file on a secure university server and accessed only by a member of research staff who is not involved in this study.

#### Allocation concealment

Participant recruitment and enrollment will be managed by research personnel who will screen for eligibility, acquire consent, and conduct baseline assessments. Randomization to an intervention group will occur after completion of the baseline assessments. Research personnel conducting assessments and analyses will be blinded to group allocation. We will not be able to blind participants or research personnel delivering the interventions and obtaining the monthly physical activity questionnaire data. Blinding will be supported by providing explicit instructions to the research personnel and participants not to discuss issues related to physical activity during the assessments.

### Experimental groups

All participants will attend four 60-min sessions each week for 6 months (i.e., 26 weeks). All sessions will have a participant to instructor ratio of 4:1, with a maximum of 12 participants per session and will be led by certified exercise instructors. Each AT, RT, or BAT session will include a 10-min warm-up, 40min training, and a 10-min cool down. To ensure fidelity across different instructors and across time, detailed protocols with pictures will be provided during instructor training. Sessions will be regularly audited by the study coordinator with standard checklists to ensure intervention content is delivered accurately and consistently. For each AT, RT, or BAT session, exercise instructors will record attendance and participation (i.e., did participant complete all components of a given session). Borg’s Rating of Perceived Exertion (RPE) [100] will be monitored at standard intervals throughout each AT, RT, and BAT session.

#### AT program

The progressive moderate-intensity AT program has been used in prior trials and improved cognitive function in older adults with MCI [101, 102]. The AT program involves a series of standardized exercise stations, including treadmills, stationary cycles, aerobic steppers, agility ladders, and non-contact boxing. Participants rotate through each station within the 40-min training duration with 1-min rest between stations. Participants will exercise initially at approximately 50% of their age specific target HRR and gradually progress to reach the target of 80% of HRR. Exercise intensity during AT sessions will be monitored via heart rate monitors and the 20-point RPE [100]. Participants will gradually progress to a target RPE of 16 to 17.

#### RT program

The RT program has been used in prior trials and improved cognitive function in older adults [102, 103]. It is designed to significantly improve muscular strength using pressurized air system and free weights to provide the training stimulus. Pressurized air system exercises will consist of triceps extension, seated row, latissimus dorsi pull downs, leg press, and hamstring curls. Free weighted exercises will consist of bicep curls, standing calf raises, wall squats, and wall push-ups.

The first 6 weeks of the RT program will focus on orienting participants with resistance training and familiarizing them with proper technique. The initial intensity of the training stimulus will be set to a weight where participants can complete 2 sets of 10–15 repetitions. Training intensity will then progress on a cyclic basis from 45 to 85% of predicted 1 repetition maximum (1RM) as determined at week 6 using an 8-repetition maximum (8RM) test. Every 4 weeks, the 8RM test is repeated and the cycle repeats.

#### BAT program

The BAT program has been used in prior exercise trials as an active control [102–104]. It is a low-intensity program consisting of stretching exercises, range of motion exercises, static balance exercises (e.g., tandem balance, single leg balance), and functional strength exercises (e.g., sit to stand). Other than bodyweight and the occasional use of light resistance bands (e.g., 2 lbs or less), no additional loading (e.g., hand weights) will be applied to any of the exercises. There is no evidence that these exercises improve cognitive function [102, 103], and this group will serve to control for known and unknown confounding variables.

### Intervention adherence

Session attendance will be recorded by the instructors and adherence will be defined as the percentage of the total sessions attended.

### Data and adverse event monitoring

A Data and Safety Monitoring Committee will be established by co-investigators who will be independent from the day-to-day conduct of the study. They will review all adverse events on a quarterly basis and will classify them based on the definitions from the January 2007 OHRP *Guidance on Reviewing and Reporting Unanticipated Problems Involving Risks to Subjects or Others and Adverse Events, OHRP Guidance* (see link)**.** The Committee will stop the study if the data are of sufficient concern (e.g., increased rate of falls as a result of the intervention). All adverse events will be reported to this Committee and if required, to the relevant university and health authority ethics boards by the study coordinator. There is no anticipated harm or compensation for trial participation.

### Statistical analyses

Initial descriptive analyses will compute percentages, mean, or median values for baseline characteristics for each of the treatment arms. Next, missing data will be examined to identify the nature of missing data. Even if data are missing completely at random, missing data will be imputed to improve statistical power using multivariate imputation by chained equations [105]. Forty imputed data sets will be created following 40 iterations of a Gibbs sampler for each imputed data set. Proper convergence of the Gibbs sampler will be confirmed by visual inspection of trace plots of each imputed variable, to ensure proper mixing and the absence of spikes or systematic trends across iterations. Analyses will be pooled across the 40 imputed data sets.

The primary analysis will be performed according to the intention-to-treat principle and entail mixed effects ANCOVA to test the main effects of AT and RT, as well as the interaction effect of AT × RT (see Fig. 2) on changes in cognitive function, as assessed by the ADAS-Cog-Plus. The ANCOVA model will use the repeatedly measured (6-month and 18-month) ADAS-Cog-Plus performance as the dependent variable; baseline ADAS-Cog-Plus score, biological sex, AT, RT, and AT × RT as independent, fixed effects variables. Furthermore, to model changes in the outcome between months 6 and 18, and to estimate distinct treatment effects at months 6 and 18, a fixed main effect of time and all interactions between time and the independent variables will be included. To account for the dependency in the repeatedly measured outcome, a random subject-level intercept will be included. Month 6 will be considered the primary endpoint and month 18 will be considered the secondary endpoint. Secondary analyses of the primary outcome will examine the interaction between biological sex and effects of AT, RT, and AT × RT. A two-tailed alpha of 0.05 will be used for each comparison (i.e., uncorrected alpha).

Secondary outcomes will be examined using identical random-effects ANCOVA models as those constructed with the primary outcome.

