### Sample size considerations

The planned sample size was determined with the aim of testing the main effects of AT and RT on changes in cognitive function, as assessed by the ADAS-Cog-Plus [50]. In computing the required sample size, we used G*Power and the sample analytic model in the statistical analyses. Unpublished data from a separate set of 96 older adults with MCI from our laboratory estimated that the correlation between baseline ADAS-Cog-Plus and the same measure collected 6 months later was approximately 0.80 [51]. This value was used to calculate the assumed residual variance in the analysis of covariance (ANCOVA) model of 0.36 (i.e., 1 − 0.80^2^). With a targeted enrolment of 216 individuals and accounting for an overall dropout of 15% (assumed to impact each intervention arm equally), we will have a power of 0.80 to detect a standardized mean difference (SMD) of 0.27 for the effect of AT or RT on cognitive function with a two-tailed alpha of 0.05 applied to each comparison [9]. The SMD of 0.27 concurs with findings from recent meta-analyses [9, 52, 53]. To detect an interaction between AT and RT with 0.80 power, the true effect size of 0.53 is required. Figure 2 depicts the 3 planned primary comparisons to examine the main and interaction effects of AT and RT.

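### With one residual variance across visits, the random-intercept model blends month-18 variance into the primary month-6 standard error; visit-specific variances should be specified

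*Protocol article*

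**What the plan says.** In the protocol article, Statistical analyses, the outcome vector holds two visits: "The ANCOVA model will use the repeatedly measured (6-month and 18-month) ADAS-Cog-Plus performance as the dependent variable". Baseline score, sex, AT, RT and AT × RT are fixed effects, and "a fixed main effect of time and all interactions between time and the independent variables will be included". The only dependency structure named is this: "To account for the dependency in the repeatedly measured outcome, a random subject-level intercept will be included". No residual variance by visit is mentioned. The time points are ranked: "Month 6 will be considered the primary endpoint and month 18 will be considered the secondary endpoint". Missing values are multiply imputed: "Forty imputed data sets will be created following 40 iterations of a Gibbs sampler for each imputed data set". The same section applies the same model to all secondary outcomes, and Mediation and moderation reuses it for sex and genotype.

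Sample size considerations rests on the month-6 variance alone. It reports that "the correlation between baseline ADAS-Cog-Plus and the same measure collected 6 months later was approximately 0.80", and "This value was used to calculate the assumed residual variance in the analysis of covariance (ANCOVA) model of 0.36".

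**The concern.** A random intercept plus one common residual variance is compound symmetry: the same total variance at month 6 and month 18. The mean model, by contrast, is fully separate by visit. The plan therefore estimates a month-6 effect from month-6 data but attaches a standard error that depends partly on how noisy month 18 is.

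There is reason to expect month 18 to be noisier once baseline is adjusted for. The Introduction cites conversion from MCI to Alzheimer's disease of 10–30% a year. Primary outcome describes a scale on which MCI sits at 0.0 and dementia at +1.0. The Discussion calls the sample heterogeneous. Uneven decline over 18 months would spread the scores and weaken their correlation with baseline. The quantities at stake are the power of the three primary month-6 tests and the type I error of the month-18 tests.

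**Working it through.** **Inputs from the protocol.** Month-6 residual variance v6 = 1 − 0.80² = 0.36. "With a targeted enrolment of 216 individuals and accounting for an overall dropout of 15" per cent gives 216 × 0.85 = 183.6, taken as N = 184 completers. Allocation is 1:1:1:1, so each main effect compares about 92 with 92. Alpha is 0.05 two-sided, SMD 0.27, stated power 0.80.

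**Input assumed.** Month-18 residual variance v18 = s² × (1 − r²), where r is the baseline-to-month-18 correlation and s is the ratio of month-18 to month-6 SD. The protocol gives neither.

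**The plan's own figure.** SE at month 6 = 2 × √(0.36/184) = 0.0885. Power = Φ(0.27/0.0885 − 1.96) = 0.863 (0.859 by noncentral t). The stated 0.80 is therefore not reproduced; it is conservative against its own inputs. That is a separate matter, but it means two reference points are needed below: 0.86 (what the inputs give) and 0.80 (what was planned).

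**Effect of one common variance.** With two visits, all time interactions and complete (imputed) data, the point estimates do not depend on the covariance structure. The random-intercept model reports the same SE at both visits:

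SE = 2 × √{[(v6 + v18)/2]/N}

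The correct values are 2 × √(v6/N) at month 6 and 2 × √(v18/N) at month 18. Real alpha at a visit is 2 × [1 − Φ(1.96 × reported SE / correct SE)]. Power at month 6 is Φ[(0.27 − 1.96 × reported SE)/0.0885].

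| r, s (assumed) | v18 | Reported SE | Reported/correct, month 6 | Reported/correct, month 18 | Alpha, month 6 | Alpha, month 18 | Power at 0.27 |
|---|---|---|---|---|---|---|---|
| 0.80, 0.9 | 0.292 | 0.0842 | 0.95 | 1.06 | 0.062 | 0.038 | 0.882 |
| 0.80, 1 | 0.360 | 0.0885 | 1.00 | 1.00 | 0.050 | 0.050 | 0.863 |
| 0.75, 1 | 0.438 | 0.0931 | 1.05 | 0.96 | 0.039 | 0.061 | 0.839 |
| 0.70, 1 | 0.510 | 0.0972 | 1.10 | 0.92 | 0.031 | 0.070 | 0.815 |
| 0.60, 1 | 0.640 | 0.1043 | 1.18 | 0.88 | 0.021 | 0.083 | 0.771 |

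If the SD also grew by 20% (r = 0.70, s = 1.2, v18 = 0.734), the month-6 SE would be 23% too large, power 0.737 and month-18 alpha 0.091.

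**Where power drops below 0.80.** Set 0.27 − 1.96 × SE = 0.842 × 0.0885. Then SE = 0.0998, the mean variance is 0.0998² × 184/4 = 0.458, v18 = 2 × 0.458 − 0.36 = 0.556, and r = √(1 − 0.556) ≈ 0.67.

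**Simulation.** In 200 REML fits per scenario with N = 184, point estimates from the random-intercept model and from separate visit regressions agreed to about 1e-15. With v18 = 0.51 the random-intercept SE averaged 0.098 at both visits, against 0.089 (month 6) and 0.105 (month 18) with separate variances. With v18 = 0.36 all were 0.088–0.089.

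**Cost of relaxing the assumption when it is true.** Error df fall from up to about 2 × 178 = 356 to 184 − 6 = 178. The critical t rises from 1.967 to 1.973, and power moves from 0.861 to 0.859.

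**The case against.** The strongest reply is that a random intercept does not by itself force equal variances. It can be combined with visit-specific residual variances. That model has three covariance parameters and matches an unstructured 2×2 whenever the covariance is positive and smaller than both variances. The article does not rule this out, and an unseen analysis plan may specify it. This stands as a limit on the wording. However, the article does state a dependency structure, and read in the ordinary way it is homoscedastic.

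Second, the direction of the error is not documented. A reader might infer that the month-6 standard error is too large. The protocol gives no month-18 SD, correlation or residual variance, so that cannot be asserted. With equal variances nothing is wrong, and with a smaller month-18 variance the direction reverses.

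Third, a reader might infer that the trial falls short of its planned power. Against the stated 0.80, that holds only if the month-18 correlation is under about 0.67 (with equal SDs). At 0.70 power is still 0.815.

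Fourth, if month 18 is the noisier visit, the primary tests err on the conservative side, so a positive month-6 result would not be called into question. The inflated error then falls on the secondary time point.

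Finally, the figures are for 184 complete cases. The planned imputation adds between-imputation variance and changes the df, so they approximate the planned analysis and are not exact for it.

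**Conclusion.** The point holds as a conditional one. On the standard reading, the month-6 and month-18 standard errors are correct only if the two residual variances happen to be equal, and nothing in the protocol supports that equality. The treatment estimates are unaffected.

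If month 18 has the larger residual variance, which is plausible but assumed here (r = 0.60–0.75, equal SDs), primary power is lost needlessly and the month-18 tests reject too often, by the amounts tabulated. If it has the smaller variance, the primary month-6 test is the anti-conservative one: a month-18 SD 10% lower at r = 0.80 gives alpha 0.062. Confidence is high on the mechanism and moderate on the size. The documents do not support saying that the month-6 error is definitely inflated, that planned power is definitely missed, or that the estimates are biased. The change is worth making because it is right whichever way the variances differ.

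**What to change.** Keep the fixed effects as they are. Replace the random intercept with an unstructured 2×2 residual covariance over months 6 and 18, or keep the random intercept and state that residual variances are visit-specific. Name a small-sample df method, such as Kenward-Roger or Satterthwaite. Use the same specification for the continuous secondary outcomes, which inherit the primary model.

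The cost is a sentence in the analysis plan, one extra variance parameter, fewer error df and, if the variances are in fact equal, about 0.2 percentage points of power. No extra data are needed.
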